## Abstract

**Background:**

Autism Spectrum Disorder (ASD) children have lower levels of participation in recreational and sporting activities when compared to their peers. Participation has been defined based on the Family of Participation-Related Constructs (fPRC) which defines participation as including both attendance and involvement, with sense of self, preferences and activity competence related to a child’s participation. Modified sports interventions such as Sports Stars can act on physical literacy and some of the fPRCs components. This study aims to assess the feasibility of the Sports Stars Brazil intervention for children with ASD.

**Methods:**

This study will be conducted with 36 participants with ASD aged 6 to 12 years old following the CONSORT for pilot and feasibility recommendation. Participants will be randomly allocated into two groups. Intervention group will receive eight, weekly Sports Stars sessions. Each session will include of sports-focused gross motor activity training, confidence building, sports-education and teamwork development. Study assessments will occur at baseline, immediately post-intervention and 20-weeks post-randomization. First, we will assess process feasibility measures: recruitment, assessment completion, adherence, adverse events and satisfaction. Second, we will investigate the scientific feasibility of the intervention by estimating the effect size and variance at the level of achievement sports-related activity and physical activity participation goals (Goal Attainment Scaling), activity competence (Ignite Challenge, Test of Gross Motor Development-second edition, Physical Literacy Profile Questionnaire, Pediatric Disability Assessment Inventory–Computer Adaptive Test—PEDI-CAT—mobility, 10×5 Sprint Test and Muscle Power Sprint Test), sense of self (PEDI-CAT—responsibility), and overall participation at home, school and community, (Participation and Environment Measure for children and young people, PEM-CY).

**Discussion:**

The results of this feasibility study will inform which components are critical to planning and preparing a future RCT study, aiming to ensure that the RCT will be feasible, rigorous and justifiable.

**Trial registration:**

The trial was registered with the Brazilian Registry of Clinical Trials database (ID: RBR-9d5kyq4) on June 15, 2022.

## 1. Background

Participation in leisure-time physical activities prepares children for a physically active life and improves health and psychosocial outcomes [1]. Despite these benefits, children with disabilities are more likely to be sedentary and experience more barriers to participation in physical activities [2]. In particular, children with Autism Spectrum Disorder (ASD) have lower levels of physical activity compared to their peers [3–5]. ASD is a neurodevelopmental disorder that affects individuals’ communication and social interaction, and includes repetitive or restricted behavior/s and interests [6, 7]. These children often experience impairments in their physical, social, cognitive and/or psychological competence, and these can pose significant barriers to their participation in sports [8]. Therefore, it is necessary to identify and promote interventions that increase participation in sports and recreational leisure-time physical activities in this population.

Participation is important as a core component of the evaluation of outcomes of children and adolescents with disabilities [9]. It is defined by the International Classification of Functioning, Disability and Health (ICF) as involvement in real-life situations [10]. More recently, the concept of participation has been extended to involve two essential components: attendance and involvement [11, 12]. The Family of Participation-Related Constructs (fPRC) defines participation as including both attendance and involvement, with sense of self, preferences and activity competence related to a child’s participation [11, 12]. Activity competence is the ability to execute the activity being undertaken according to an expected standard, includes cognitive, physical and affective skills and abilities [11, 12], where can be measured: (1) abilities that the child can use in a daily environment, (2) ability of the child within a structured environment like that created for test-taking and (3) abilities the child uses in everyday settings [13, 14]. Attendance is characterized as “being present” and can be measured as frequency or diversity of activities that an individual participates [11, 12]. Involvement refers to the subjective experience of participation during attendance, including elements such as engagement, persistence, social bonding, and affection level [11, 12].

When considering participation in sports and recreational activities, activity competence can be associated with physical literacy. Physical literacy describes the skills that one needs to engage in enjoyable leisure-time physical activities throughout life, in four domains: 1) physical (e.g., locomotor skills); 2) psychological (e.g., motivation); 3) social (e.g., relationships); and 4) cognitive (e.g., content knowledge) [15–17]. The interaction between the fPRCs and physical literacy provides a greater understanding of the participation of children with ASD in physical and sports activities and provides guidance for future participation-based research.

Recently, Clutterbuck, Auld and Johnston [18] developed Sports Stars, a modified group sport intervention held in the community environment. Sports Stars has shown to be effective in improving preferred sports-related activity and physical activity participation (attendance and involvement) goals and activity competence for ambulant Australian children with cerebral palsy (CP) compared to usual care [18]. Furthermore, parents and therapists perceived that Sports Stars improved children’s physical literacy across all domains, including the physical, social, psychological, and cognitive competence needed for sports participation, and that Sports Stars would be their intervention of choice for children with sports focused goals [19].

The prevalence and rate of diagnosis of children with ASD has been growing in recent years [20, 21]. According to the Brazilian Society of Pediatrics (SBP) [22], in Brazil, children with ASD frequently receive a late diagnosis and consequent delayed access to intervention, which might compromise their development [22]. There are significant advances in the international public policies for this population [20, 21]. However, in Brazil, laws were only recently introduced to guarantee the rights of people with ASD, for example to participate in sports and leisure activities (Laws: 12.764/2012–13.146/2015) [23, 24]. Despite the evidence suggesting that participation of people with ASD in leisure-time physical activities and group sports improves their socialization skills, communication, development of independence, motor skills and cardiovascular fitness, up to now, this is addressed by just one initiative by the Brazilian Government (entitled TEAtivo) [25–28]. Larger efforts are needed to developed appropriate interventions, such as Sports Stars, to improve physical activity levels and promote participation in sports and physical recreation for this population [29, 30]. However, while the effectiveness and feasibility of Sports Stars Brazil is under investigation in children with CP by our research group [31, 32], its feasibility in other conditions such as ASD is still unknown. This paper presents a feasibility Randomized clinical trial (RCT) protocol aiming to assess the feasibility of the Sports Stars Brazil intervention for children with ASD as articulated by Thabane et al. (2010) framework [33]. This framework encompasses that the aim of a feasibility study might be linked to one or more of the following four classifications: process, resources, management and scientific. In this study, we will focus on two feasibility classifications:

First, we will assess the process of feasibility that will determine the ability to enroll participants, the assessments completion rates, as well as adverse effects, satisfaction and adherence. To this purpose, a priori success criteria will be established when appropriated. Second, we will evaluate the scientific feasibility for estimating the effect size and variance of nine outcomes aligned with the fPRCs components.

## 2. Methods and analysis

### Study design

This will be a prospectively registered, open, two arm, pilot RCT. This manuscript was written in accordance with the SPIRIT (Standard Protocol Items: Recommendations for Interventional Trials) guidelines [34] (see S1 Checklist). Forthcoming publication of trial results will be reported according to reporting standards for pilot and feasibilities studies (i.e., Consolidated Standards of Reporting Trials—CONSORT), (see S2 Checklist) [35]. The schedule with assessment at different points in time is shown in Fig 1.

**Fig 1 pone.0291488.g001:**
[figure not shown]
Time schedule of enrolment, interventions, and assessments on participant outcome inspired by the SPIRIT 2013 reporting guidelines [34]. Autism classification system of functioning: social communication—ACSF: SC; Participation and Environment Measure for children and young people -PEM-CY; GAS—Goal Attainment Scaling; Physical Literacy Profile Questionnaire- PLPQ; Pediatric Disability Assessment Inventory–Computer Adaptive Test—PEDI-CAT; Test of Gross Motor Development-second edition–TGMD-2; 10×5 Sprint Test -10x5 ST and Muscle Power Sprint Test–MPST.

SPIRIT schedule of assessments at different time points

### Study setting

The study will be conducted in open spaces and sports courts/facilities of a university in the city of Belo Horizonte, Brazil.

### Eligibility criteria

Inclusion Criteria

Children aged 6 to 12 years at the beginning of the intervention;Diagnosed with ASD according to medical report, and classified at support levels I or II by the Autism classification system of functioning: social communication ACSF:SC [36];Both genders.

Exclusion Criteria

Participants with cognitive, behavioral, or clinical limitations that prevent them from following instructions and safely participating in group physical activity;Who have undergone surgery or fractures in the last 6 months.

### Procedures

Children with ASD will be recruited through advertisement, radio spots, social media networks, as well as recruited by convenience from public or philanthropic institutions and private rehabilitation clinics in Belo Horizonte, Brazil. All eligible individuals will receive clarifications regarding the objectives of the study and will sign a statement of informed consent prior to participation. Participants characteristics will be collected. Finally, two blinded researchers will collect the outcome data at baseline, 8 weeks after randomization, and the follow-up evaluation. All assessments will be repeated by the same assessors.

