Activity and physical activity participation goals will be evaluated by the Goal Attainment Scaling–GAS [43, 44]. GAS is patient centred and has been widely used to quantify the achievement or fulfillment of goals previously defined in an intervention program [43–46]. In this study, goals will be selected by caregivers. In order to increase responsiveness, validity and reliability, three goals that can be affected by the treatment will be identified [47]. The first refers to performance of a sport-related motor activity, the second and third refers to attendance and involvement in leisure-time physical activities during sports or physical recreation participation (see example in Table 1). All GAS’ will be shared among caregivers and interventionists at baseline by another non-blinded assessor.

**Table 1 pone.0291488.t001:** Goal attainment scale examples.

Score	Meaning	Sports-related activity example	Attendance of physical activity participation	Involvement of physical activity participation
		*Parent’s goal*: *To dribble a soccer ball with control along the soccer field*	*Parent’s goal*: *To participate in soccer classes at least twice in a week*	*Parent’s goal*: *To be engaged at least 30 minutes when participates in school’s sports activities of one-hour duration*
**-2**	Current level	Dribbles a soccer ball during 4 meters of the soccer field without lose control of the ball	Does not participate in soccer classes in a week	Is not engaged at all during school’s sports activities
**-1**	Less than expected	Dribbles a soccer ball during 6 meters of the soccer field without lose control of the ball	Participate in soccer classes one day in a week	Is engaged in 15 minutes during school’s sports activities
**0**	Expected to achieve	Dribbles a soccer ball during 10 meters of the soccer field without lose control of the ball	Participate in soccer classes two days in a week	Is engaged in 30 minutes during school’s sports activities
**+1**	More than expected	Dribbles a soccer ball during 12 meters of the soccer field without lose control of the ball	Participate in soccer classes three days in a week	Is engaged in 45 minutes during school’s sports activities
**+2**	Much more than expected	Dribbles a soccer ball during 14 meters of the soccer field without lose control of the ball	Participate in soccer classes four days in a week	Is engaged in 60 minutes during school’s sports activities

*Activity Competence and sense of self*

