***Ignite Challenge*:** Measures accuracy and speed of locomotor and object control skills necessary for sports and active recreation activities [48]. It is a 13-item measure that can be used in children with ASD classified at ACSF levels I and II. The instrument total raw score is converted in percentage points. The higher the score, the better the performance. It can include “picture cards” for each test item to supplement evaluators’ demonstrations and improve understanding of each test item [49–51]. The *Ignite Challenge* has demonstrated excellent inter-rater (ICC = 0.91 (95% = 0.93, 0.99), intra-rater (ICC = 0.96, 95% = 0.90, 0.98) and rest-test (ICC = 0.91, 95% = 0.84, 0.95) reliability in Australian children with ASD (n = 47) [51].**Test of Gross Motor Development-2—TGMD-2:** Is used in children up three to 10 years, it assesses accuracy and quality of 12 fundamental motor skills, six of which are locomotor skills and six are object control skills. The total scores of each subtest are summed and represented as raw scores, which can be converted into motor quotients [52]. The TGMD-2 was validated and reliable for typical Brazilian children in the study by Valentini et al. [53] and has been used in children with ASD [54, 55]. Furthermore, it has been seen as a responsive measure in the Australian Sports Stars in children with CP [18]. Reliability of the TGMD-2 for children with ASD is currently being evaluated by our research group (ongoing study).**10×5 Sprint Test–(10×5ST) and Muscle Power Sprint Test (MPST):** The 10×5ST assesses agility [56, 57]. In the 10×5ST, participants need to run 5 m separated by 2 cones, 10 times continuously, making turns in the cones that mark the end of the five meters [57]. The 10×5ST has excellent inter-observer and test-retest reliability (ICC = 1.00 and 0.97) and good reported construction validity. An increase in agility of 3.2 seconds is considered a real change [54]. Participants muscle power will be evaluated by the Muscle Power Sprint Test–MPST [54]. The MPST measures muscle power by asking the participant to run as fast as possible for 15 m, 6 times, with a 10 second interval between each sprint. The MPST has high inter-observer and test-retest reliability (ICC = 0.97 and 0.99) for ambulant children with CP [56]. Reliability of the MPST and 10x5ST for children with ASD is currently being evaluated by our research group (ongoing study).**Pediatric Evaluation of Disability Inventory—Computer Adaptive—PEDI-CAT ASD:** Will be used to assess the domains of mobility (activity competence) and sense of self (responsibility) [58]. In the PEDI-CAT domain mobility the four-point scores are based on different levels of difficulty. The responsibility domain ranks items on a five-point scale, describing the division of responsibility between the caregiver and the child in managing complex, multi-step life tasks. The PEDI-CAT was adapted and presented reliability to be used by children with autism [59]. It was translated and culturally adapted for the Brazilian population aged 0–21 years [60].**Physical Literacy Profile Questionnaire–PLPQ:** Assesses the components of physical literacy (physical, cognitive, social and psychological) of children [61]. The questions are related to performance and satisfaction in the physical, social, psychological and cognitive competencies. Each item assesses performance on a scale of 0 to 2 and each item assesses the child/adolescent/young adult’s performance satisfaction on a scale of 1–10 points. The higher the score, the higher the level of performance and satisfaction. The QPAF is in the process of being validated by our research group, preliminary data showed good test-retest reliability for children with CP (ICC = 0.84; IC [95%]: 0.74–0.91) (data not published yet) [61].

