*Overall Participation at home, school and community*
**Participation and Environment Measure for Children and Youth—PEM-CY:** Will be used to assess participation at home, school and community [62, 63]. The measure identifies attendance and involvement of children in activities carried out at home, at school and in the community, as well as the characteristics of these environments that influence participation in six parts: frequency of participation, involvement of participation, desire to change participation, support for the environment, support for the environment and environmental resources [64, 65]. The PEM-CY has moderate to good internal consistency and test-retest reliability indices [62] and was translated and culturally adapted for the Brazilian population [58]. The PEM-CY it has been used as an outcome measure to assess the effects of participation interventions on individuals with ASD [66, 67].

*Randomization and blinding*. Children (n = 38) will be randomized into 2 groups (Sports Stars Brazil intervention and control group). Randomization will occur when 8 to 10 the child has been recruited and the allocation ratio will be 1:1. The randomization will be performed using a computer-generated random sequence to ensure equal allocation to each group. This sequence will be used to randomize children into the immediate group, or the control group. A new sequence will be used for each subgroup randomization until 36 children are allocated, or no further participants can be recruited. All assessments will be performed before the allocation of each subgroup. Thus, the use of the block randomization method is unlikely to increase the probability of identifying the allocation of participants.

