An independent researcher, not involved in recruitment or data collection and without direct contact with those involved in this research, will perform all randomization steps. The randomization process and allocation of participants will be supervised by the independent investigator. Due to the intervention characteristics of this study, it is not possible to blind participants and interventional therapists to group allocation. In order to minimize bias, the children and their caregivers will be instructed to not tell the assessors which group they are in until after all their baseline assessments were completed. Furthermore, all the two blinded assessors will be asked to indicate if they know which group (control or intervention, and if so to cite the source of unblinding). This will permit to report the success of blinding. The statistician will be blinded to the group allocation until the completion of the analyses.

The possible contamination of information between the groups will also be evaluated. For this, the following questions will be asked. 1) Have you talked to other participants in this study about the intervention they are receiving? 2) If so, did your attitude towards the intervention change after talking to one of the participants in the other group? 3) Did you have any changes related to physical activity after the first contact with our project? 4)Are any of the participants in the other group aware of the type of intervention you were receiving in this study?

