### Data integrity and management plan

Research data will be collected by two research assistants who will be trained to collect and manage it. Participant identifiers (including name, address, contact information and other personal information) will be removed from the survey data and stored in another file. The data will be entered into Microsoft Excel and SPSS. Survey data will be monitored weekly and any errors in input will be identified (if any) and amended. Consent forms will be stored in the office of the School of Physical Education, Physiotherapy and Occupational Therapy at the Federal University of Minas Gerais along with other research data files.

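### Nothing stated keeps the blinded raters of the motor tests away from participation answers that can suggest the arm, and the only non-disclosure instruction ends at baseline

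*Protocol article*

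**What the plan says.** **Who collects the data.** Procedures states that "two blinded researchers will collect the outcome data at baseline, 8 weeks after randomization, and the follow-up evaluation", and adds that "All assessments will be repeated by the same assessors". The Data integrity and management plan again names a team of two: "Research data will be collected by two research assistants who will be trained to collect and manage it". No instrument is exempted.

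**What they collect.** The nine scientific-feasibility outcomes mix two kinds of measure.
- Four are performance tests. Ignite Challenge covers accuracy and speed. TGMD-2 is rated on movement: "it assesses accuracy and quality of 12 fundamental motor skills". The 10×5 Sprint Test and the Muscle Power Sprint Test are running tests.
- The other five are goal or questionnaire measures: GAS, PEM-CY, PLPQ and the two PEDI-CAT domains. Of PEM-CY the article says: "The measure identifies attendance and involvement of children in activities carried out at home, at school and in the community". Of the three GAS goals, "the second and third refers to attendance and involvement in leisure-time physical activities during sports or physical recreation participation".

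**GAS handling.** The goals are "shared among caregivers and interventionists at baseline by another non-blinded assessor". The article does not say who rates them later.

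**Protection of blinding.** Under Randomization and blinding, participants and therapists are acknowledged to be unblinded. Families are "instructed to not tell the assessors which group they are in until after all their baseline assessments were completed". The two assessors are asked whether they know the arm and how they learned it.

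**The concern.** In an open trial, assessor blinding is the main protection for outcomes that someone has to judge. Here that means chiefly TGMD-2 and Ignite Challenge. The protection fails if the rater learns or guesses the arm before scoring. Conversation with an unblinded family about what sport the child has been doing is an obvious way for that to happen.

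What is at stake is the effect size and variance that the pilot is meant to pass on to the definitive RCT. A rater who suspects that a child received Sports Stars may score more generously. The resulting effect size would be too large, and a later trial planned on it would be too small.

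**Working it through.** The article gives no unblinding rate and no size of observer bias, so there is no figure to reproduce. The check sets the statements side by side.

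**1. Is there a route to unblinding at 8 weeks?** The intervention is eight weekly one-hour group sessions of soccer, handball, basketball and athletics (Interventions, Sports Stars Brazil group). The 8-week visit follows directly. PEM-CY covers community attendance, and the GAS attendance example in Table 1 counts days per week in soccer classes. The respondents know the arm. An honest answer can therefore point to it. For PEM-CY this follows from the statement that the blinded pair collect the outcome data. For GAS it holds only if the pair also collect the later GAS ratings.

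**2. Does it extend to 20 weeks?** Not by the same mechanism. Sports Stars has ended by then, and controls are offered it only after follow-up (Usual care or control group). The link is memory: the same assessors repeat all assessments, so knowledge gained at 8 weeks can be carried forward. The direct route covers at most the 36 eight-week visits. The 36 later visits are exposed only through carry-over.

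**3. Does the non-disclosure instruction close the route?** It lasts until baseline is complete. The randomization text places assessment before the allocation of each subgroup, which can only mean the baseline assessment. In order:
- baseline: instruction in force, no arm assigned;
- allocation: an arm now exists, instruction has lapsed;
- 8 and 20 weeks: an arm exists, no instruction in force.

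As written, the instruction covers only the period in which there is nothing to disclose.

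**4. Does the blinding question close it?** No. It records knowledge and its source. The article does not tie it to a moment in the visit, so an answer given at the end cannot show whether the rater knew the arm when scoring.

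**5. Which results are exposed?** Four of nine outcomes are performance tests. TGMD-2 and Ignite Challenge are the most exposed. The two sprint tests leave less room for judgement. The two success criteria (≥10% response and ≥80% completion) depend on no rating.

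**6. Consequence for planning, as illustration only.** Required sample size varies as 1/d². If the true d were 0.50 and the pilot gave 0.60 (both assumed), the planned size would fall by 1 − (0.50/0.60)² = 1 − 0.694 = 0.306, about 31%.

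**The case against.** The strongest reply is that much of this is inferred from silence.

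- **Same person, same child.** A reader might infer that one assessor takes both the questionnaires and the motor tests for a given child. The article does not say so. The two could divide the work, or forms could be self-completed, and an article may leave such detail to the full protocol. This stands, so the point is that no separation is stated, not that one person does both.
- **Answers reveal the arm.** This is too strong. PEM-CY spans home, school and community, the GAS examples concern soccer classes and school sport, and control children may do these too. The answers can suggest the arm; they need not disclose it.
- **GAS.** The only named handler is non-blinded, and only at baseline. Who rates GAS later is open.
- **Size.** One could multiply an assumed share of unblinded visits (25–75%) by an assumed shift (0.1–0.3 SD) and get 0.25 × 0.1 = 0.025 to 0.75 × 0.3 = 0.225. Neither input comes from the documents, so the product is not evidence that the bias passes the plan's 0.20 threshold.
- **Consequence.** No significance tests are planned. With 18 per arm the standard error of d is roughly √(2/18) = 0.33, so the 95% interval is about ±0.65. That is wide, but it describes sampling error only and does not cover a systematic shift.
- **Recording unblinding is itself useful in a pilot.** True, and more so if the question comes directly after the tests.

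None of this answers the timing of the non-disclosure instruction. That is a defect in the stated text, even if only a drafting slip.

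**Conclusion.** The concern holds in a limited form. The article gives all outcome data to one blinded pair, states no separation between performance tests and participation measures, and has a non-disclosure instruction that lapses before any arm exists. Together these leave a plausible, unguarded route to unblinding at 8 weeks, with possible carry-over to 20 weeks.

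The size of any bias cannot be derived from the documents. The likely direction favours Sports Stars. It falls mainly on TGMD-2 and Ignite Challenge and less on the timed tests. It affects only the effect sizes for scientific feasibility.

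The conclusion assumes that no unshown document separates the tasks. If one does, a clarifying sentence settles that part, but the non-disclosure instruction would still need correcting. The change is worth making because it is cheap and protects the outcomes for which blinding can work.

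**What to change.** 1. **Procedures.** State that at the 8-week and 20-week visits the blinded assessors administer, score and lock the four performance tests before any caregiver-reported instrument, contamination question or satisfaction form is opened. They answer the blinding question directly after the performance tests.
2. **Randomization and blinding.** Extend the instruction to families not to disclose their group through the last follow-up assessment.
3. **Where feasible,** have caregivers complete the forms themselves, away from the performance raters. State who rates GAS after baseline.

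Fixing the order does not by itself prevent carry-over from 8 to 20 weeks, because the same assessors return. Item 3 reduces that.

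The cost of items 1 and 2 is protocol wording and a fixed visit order, with no extra staff. Item 3 means less interviewer help with the forms. Using the non-blinded assessor at later visits is optional and should not be assumed free, since the article names that role only for a baseline task.
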